#### Measuring morbidity and lifestyle

Alcohol abuse or dependency: the AUDIT is a 10-item questionnaire designed to screen for excessive drinking. It takes 2 minutes to complete, with scores of 15 or greater indicating harmful alcohol use or dependency [36]Medical morbidities, medications and lifestyle: we will collect information about demographics, lifestyle (smoking, alcohol use, body mass index), common medical conditions diagnosed by a doctor, and medications used (including use of illicit substances). This questionnaire takes approximately 5–10 minutes to completeDetails of surgery: we will record the type of surgery and total length of surgical procedure including duration on bypass (if applicable)Medications: we will record participants’ medications on admission and discharge. We will also record the use of all psychiatric medications during hospitalizationReferral to mental health or geriatric services during admission will be recordedLength of stay (LOS): we will record total hospital stay duration and intensive care unit (ICU) length of stay in hours for participants discharged alive from hospitalDestination post discharge: we will record destination post discharge for all participants and, for the purposes of analysis, will group them into “discharge to usual place of residence” versus “discharge to other places.” Participants who die following cardiac surgery will form a separate groupCognition: this will be measured with the TICS-m. The TICS-m is a brief, widely used telephone assessment instrument with good reliability and validity to screen for dementia and cognitive impairment in older people [40]. It can be rated in person or by telephone. It consists of 13 items measuring various aspects of cognitive function yielding a total score of 50. Scores ≤27 indicate the presence of clinically significant cognitive impairment. Cognitive function will be measured at baseline, discharge and 3 months after surgery. The TICS-m was chosen to allow us to assess participants’ cognition 3 months after surgery in the comfort of their own homes. We deliberately chose this approach to reduce participant burden and improve study retention. In addition, many Western Australian patients live in country areas so that in-person attendance would be difficultDepressive and anxiety symptoms: we will measure depressive and anxiety symptoms at baseline, discharge and at 3 months with the Hospital Anxiety and Depression Scale (HADS) [41]. This is a self-report scale of 14 items in total that gives sub-scores for both depression and anxiety

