### Objectives

The primary outcome of interest for this study is the difference in the incidence of delirium (as determined by the CAM and *Diagnostic and Statistical Manual of Mental Disorders, version 5* (DSM-5) criteria) between the placebo and melatonin groups within 7 days following cardiac surgery. Secondary outcomes of interest include the difference between groups in the severity and duration of delirious episodes, hospital length of stay and referrals to mental health services during the admission. In addition, we will assess for differences in mood and anxiety symptoms and cognitive performance at discharge and at 3 months after surgery.

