## Methods

### Participants and setting

We will recruit 210 participants undergoing elective or semi-elective cardiac surgery in Perth, Western Australia. All outpatients undergoing elective cardiac surgery attend the pre-assessment clinics before admission (usually a week prior). Potential participants will be approached during this clinical review and offered an opportunity to participate in the study. In addition, we will approach patients admitted to cardiology and general hospital wards awaiting surgery on a semi-elective basis; e.g., stable patients admitted with a myocardial infarction or unstable angina deemed suitable for surgical intervention.

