### Interventions

Eligible participants will be randomly allocated to treatment with 3 mg melatonin or matching placebo for seven consecutive nights, beginning 2 nights prior to the surgery. The contents of each capsule will be administered via a nasogastric tube for those who are unable to swallow.

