
### Participant timeline and recruitment

Table 1 shows the trial assessment schedule and Fig. 2 summarizes the recruitment and the flow of participants in the trial. Participants will be approached in pre-assessment clinics (all patients attend these a week or so prior to the scheduled surgery) and general hospital wards for those already hospitalized and awaiting surgery (i.e., semi-elective cases). Enrolled participants will be seen daily following their surgery with the primary outcome of interest being the difference in the incidence of delirium between the two groups. The final hospital assessment will occur on day 7 following surgery or the day of discharge (whichever comes first). Participants will be followed up one more time at 3 months after surgery to assess for the presence of delirium and to measure cognitive function.

**Table 1 Tab1:** Summary of trial assessment schedule

	Baseline	Daily	Discharge/7 days post surgery	3 months
Demographics	x			
Medical comorbidities	x			
Medications	x		x	
Surgery details			x	
Referral to mental health and geriatric services			x	
AUDIT	x			
LOS			x	
Adverse events	x		x	
CAM	x	x	x	x
MDAS	x	x (if required)	x (if required)	x (if required)
TICS-m	x		x	x
HADS	x		x	x

*AUDIT* Alcohol Use Disorders Identification Test, *CAM* Confusion Assessment Method, *HADS* Hospital Anxiety Depression Scale, *LOS* length of stay, *MDAS* Memorial Delirium Assessment Scale, *TICS-m* Telephone Interview for Cognitive Status-modified

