### Allocation, randomization, blinding and compliance

Participants will be randomized to treatment with melatonin or placebo in a ratio of 1:1 according to a list of computer-generated random numbers in permuted blocks ranging from 8 to 12. This strategy decreases the risk of unblinding of participants in one particular block if, for some reason, the group membership of one of its members is disclosed. The list will be generated and maintained by an independent biostatistician.

The pharmacy will dispense melatonin or placebo. Melatonin and placebo will be administered as oral capsules that have the same size, weight, color, texture and taste. The active medication will consist of 3 mg melatonin. These will be manufactured in batches every 12 months with 6-monthly stability testing performed for weight, disintegration, impurities and appearance. The pharmacy will be responsible for dispensing all study medications, which will be included on the patient medication chart as per usual hospital practice. Unblinding will only occur once the final endpoint of interest is collected from the last participant in the trial. Compliance will be encouraged through a telephone call to each participant 2 days prior to his or her scheduled surgery date. Participants will be reminded to take their tablets and will be asked to bring the remainder into hospital for use following their surgery. Participants will be given ten tablets to allow for the possibility of surgery being postponed once they have commenced taking the trial medication. We will record all incidences where participants take extra tablets beyond the scheduled seven. Treatment adherence will be determined by the systematic review of medication charts upon discharge and by pill count. Use of sedative/psychotropic medications outside of the study protocol will also be recorded.

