## Discussion

Delirium is a major issue for the medical community and is associated with universally poor outcomes for patients, their families and the health care system. Delirium is particularly problematic in surgical populations and may complicate up to 42 % of patients undergoing major cardiac surgery. Identification and management of sufferers is often complex and many individuals are missed. Prevention of this common condition is, therefore, essential. This trial will determine if melatonin is able to reduce the incidence and duration of delirium following cardiac surgery and also reduce the burden of other associated factors such as cognitive decline, hospital length of stay and anxiety and depressive symptoms.

The design of this trial has strengths and weaknesses that merit comment. It has not yet been established what dose of melatonin may be optimal for the prevention or treatment of delirium. The trials conducted to date have utilized a variety of doses ranging from 0.5 to 5 mg [30, 31, 33] and one that used 8 mg of the melatonin agonist ramelteon [34]. The trial by de Jonghe and colleagues showed the 3-mg dose used in the study to be both well-tolerated and safe [33], as did another trial in tracheostomized intensive care patients that additionally showed that 3 mg melatonin successfully increased blood levels 1000-fold [42]. A number of other trials have confirmed the safety and tolerability of a 3-mg dose in populations with varying medical morbidities and age ranges [43–46]. We will exclude participants with cognitive impairment, given the possible difficulties with consent and the ability to follow the trial protocol. We understand, however, that this may reduce the overall incidence of delirium in our sample, as pre-existing cognitive impairment is a strong predictor of delirium.

This trial will be restricted to adults aged 50 and older because the incidence of delirium is higher in later life. We will also exclude participants undergoing emergency surgery because of the ethical requirements for recruitment and informed consent. The study will be limited to participants with sufficient English skills to be able to participate in the assessments and complete the study questionnaires. All of these factors could potentially decrease the generalizability of our findings.

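### Length of stay is measured as total hospital stay in survivors: waiting days before dosing cost precision, and dropping deaths selects on an event after randomisation

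*Protocol article*

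**What the plan says.** The Objectives section of the protocol article lists among the secondary between-group outcomes "hospital length of stay and referrals to mental health services during the admission". The Discussion section says that the trial will show whether melatonin lessens the burden of "cognitive decline, hospital length of stay and anxiety and depressive symptoms".

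The definition is under Measuring morbidity and lifestyle: "we will record total hospital stay duration and intensive care unit (ICU) length of stay in hours for participants discharged alive". The next item there, discharge destination, covers every participant and gives deaths their own category. Length of stay has no matching rule.

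Three other sections bear on what a total stay contains:

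- Participants and setting: "we will approach patients admitted to cardiology and general hospital wards awaiting surgery on a semi-elective basis". Participant timeline and recruitment confirms that these people are found on "general hospital wards for those already hospitalized and awaiting surgery (i.e., semi-elective cases". Elective participants are approached at an outpatient clinic about a week before surgery.
- Interventions: study drug is given "for seven consecutive nights, beginning 2 nights prior to the surgery".
- Allocation, randomization, blinding and compliance: assignment is 1:1 "according to a list of computer-generated random numbers in permuted blocks ranging from 8 to 12". No stratification by admission type is described.

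**The concern.** Two features of the definition work against its use as a treatment comparison.

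**Start of the clock.** On its natural reading, a total stay runs from admission. For a semi-elective participant, admission comes before enrolment and usually before the first dose. Those waiting days depend on the admission and the theatre list, not on the assigned capsule. For an elective participant, dosing can begin at home, so there is little or no such wait. The same variable then has a different time origin in two kinds of participant, and the difference enters the comparison as variation unrelated to treatment.

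**Survivors only.** Whether a participant leaves hospital alive is settled after randomisation. If one arm has more in-hospital deaths, and the deaths fall among people who would have stayed long, that arm loses its longest stays and looks better. A larger sample does not cure this.

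At stake is the precision and interpretability of one secondary outcome, plus ICU stay for the second feature. The primary delirium comparison is not affected.

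**Working it through.** The article states no mean, SD, target difference or power for length of stay, and no mortality, so there is no figure to reproduce. Everything below except the numbers randomised (105 per arm, 210 in total, from the Sample size section) is an assumption, shown as a range.

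**1. Precision lost to waiting days**

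Let the postoperative stay have SD 4 days (variance 16). Let a proportion p of participants be semi-elective, with a preoperative wait of mean m and SD s days. Assume no preoperative stay in elective patients, and a wait independent of the postoperative stay. Then

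Var(total) = 16 + p·s² + p(1−p)·m²

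and, for an unadjusted comparison of means, the effective sample is 16 / Var(total).

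| Case | p | m | s | Var(total) | Effective sample | Lost |
|---|---|---|---|---|---|---|
| Low | 0.20 | 3 | 2 | 16 + 0.8 + 1.44 = 18.2 | 88% | 12% |
| Central | 1/3 | 5 | 3 | 16 + 3 + 5.56 = 24.6 | 65% | 35% |
| High | 0.50 | 7 | 4 | 16 + 8 + 12.25 = 36.3 | 44% | 56% |

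In the central case the standard error grows by √(24.6/16) = 1.24, that is, by 24%.

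Adjusting for admission type removes the p(1−p)·m² term but not p·s². In the central case the variance is then 16 + 3 = 19, and 1 − 16/19 = 16% is lost. For the low and high cases the losses become 1 − 16/16.8 = 5% and 1 − 16/24 = 33%.

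**2. The same point as power**

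Take postoperative SDs of 3 and 5 days, with 105 per arm. The difference giving 80% power is (1.96 + 0.84) × SD × √(2/105), or 1.16 and 1.93 days. Analyse total stay instead, unadjusted:

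- Mildest case: SD 5, 20% semi-elective, wait mean 4 (SD 3). Variance is 25 + 1.8 + 2.56 = 29.4, total SD 5.42, power 73%.
- Most severe case: SD 3, 50% semi-elective, wait mean 7 (SD 5). Variance is 9 + 12.5 + 12.25 = 33.8, total SD 5.81, power 30%.

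Counting from surgery restores 80% in both.

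**3. Deaths**

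In-hospital mortality of 1% to 3% would remove 210 × 0.01 to 210 × 0.03, about 2 to 6 participants. At 5% it would be about 11.

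To see how selection acts, suppose 20% of participants would stay 20 days, the rest 8 days, all deaths fall in the long-stay group, and treatment has no effect on stay. With mortality d, the survivors' mean is [(0.2 − d) × 20 + 0.8 × 8] / (1 − d).

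- Control 4%, melatonin 2%: 9.6/0.96 = 10.00 against 10.0/0.98 = 10.20. Melatonin appears 0.20 days longer.
- Control 5%, melatonin 1%: 9.4/0.95 = 9.89 against 10.2/0.99 = 10.30. Melatonin appears 0.41 days longer.
- 2% in both arms: no difference.

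The arm with fewer deaths is penalised, and the shift vanishes when mortality is equal.

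**The case against.** **The figures are assumed and depend on the analysis.** This stands. The article names no analysis for length of stay, and adjustment, a log scale or ranks would each change the loss. Adjustment for admission type roughly halves it in the central case. None of these removes the variation in waiting time among semi-elective participants.

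**The word total may only mean ward plus ICU.** It stands beside ICU stay, the start point is not spelled out, and a full protocol might set the clock. This is possible, but nothing in the article starts the clock at surgery or randomisation, and admission is the natural reading. Total stay is a fair measure of resource use, which is a reason to keep it as a description.

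**Reporting stay in survivors is a common and openly stated convention.** Emergency surgery is excluded, deaths stay visible under discharge destination, and nothing in the document suggests that mortality will differ by arm. That supports calling the bias probably small. It does not make the comparison one of everyone randomised.

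**A reader might infer that stay is cut off at day 7.** Table 1 places length of stay in the column for discharge or day 7, and the text says "The final hospital assessment will occur on day 7 following surgery or the day of discharge (whichever comes first". That sentence governs the bedside assessment, and the column labels a visit. A total stay for someone discharged alive can be known only at discharge, so the documents do not support a truncation finding.

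**A reader might add chance imbalance in admission type as a further error.** That imbalance is already the p(1−p)·m² term; adding it again would count it twice.

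**Conclusion.** The definition is weaker than it needs to be, in two separate ways.

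- **Waiting days cost precision.** They are balanced in expectation by randomisation and do not bias the comparison. The loss runs from about 12% to 56% of the effective sample, and is 35% in the central case or about 16% after adjustment for admission type. These figures rest wholly on the assumed SD, waits and semi-elective share. The claim that treatment cannot act applies only to days before dosing; up to two preoperative nights are on study drug. ICU stay is little affected.
- **The survivor restriction can bias.** This needs mortality to differ by arm. With low mortality the shift is probably small: 0.20 days in an illustration with 4% against 2%.

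A reader might infer that the survivor restriction breaks the trial's own intention-to-treat rule. It does not: Statistical methods states that rule for the primary outcome only. This is a weakness of design, not a contradiction.

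The change is worth making because it is cheap and the outcome is a named one. No sample size, stated power or primary conclusion depends on it.

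**What to change.** For the treatment comparison, define length of stay as hours from the end of surgery to live discharge, in all randomised participants who have surgery. Keep deaths in the comparison, either by analysing time to live discharge with death as a competing event, or by a rank test with deaths ranked worst. Handle deaths in the same way for ICU stay. Report total hospital stay descriptively.

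The cost is outcome wording. Surgery and discharge times should be available in the hospital record, and no extra visits or participants are needed. The Trial status section says that recruitment has not begun, so the change can be made before any data exist. There is one small downside: the main result is no longer a simple mean total stay for costing, although the descriptive total still serves that purpose.

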
### Participant timeline and recruitment

Table 1 shows the trial assessment schedule and Fig. 2 summarizes the recruitment and the flow of participants in the trial. Participants will be approached in pre-assessment clinics (all patients attend these a week or so prior to the scheduled surgery) and general hospital wards for those already hospitalized and awaiting surgery (i.e., semi-elective cases). Enrolled participants will be seen daily following their surgery with the primary outcome of interest being the difference in the incidence of delirium between the two groups. The final hospital assessment will occur on day 7 following surgery or the day of discharge (whichever comes first). Participants will be followed up one more time at 3 months after surgery to assess for the presence of delirium and to measure cognitive function.

**Table 1 Tab1:** Summary of trial assessment schedule

	Baseline	Daily	Discharge/7 days post surgery	3 months
Demographics	x			
Medical comorbidities	x			
Medications	x		x	
Surgery details			x	
Referral to mental health and geriatric services			x	
AUDIT	x			
LOS			x	
Adverse events	x		x	
CAM	x	x	x	x
MDAS	x	x (if required)	x (if required)	x (if required)
TICS-m	x		x	x
HADS	x		x	x

*AUDIT* Alcohol Use Disorders Identification Test, *CAM* Confusion Assessment Method, *HADS* Hospital Anxiety Depression Scale, *LOS* length of stay, *MDAS* Memorial Delirium Assessment Scale, *TICS-m* Telephone Interview for Cognitive Status-modified

**Fig. 2 Fig2:**
[figure not shown]
Summary of participant timelines. The figure summarizes the enrollment procedure and time commitment for participants

### Sample size

The primary outcome of the proposed trial is the development of delirium within 7 days of surgery. We based our sample size on the trial of Al-Aama and colleagues [31]. They reported a 15.6 % absolute reduction (19.2 % versus 3.6 %, *p* < 0.02) in the incidence of delirium in their sample. Assuming a 15.6 % absolute risk reduction in our patients with a conservative 25 % incidence of delirium in the control group and an incidence of 9.4 % in the intervention group, we will require 91 participants per group (182 participants in total) to detect a difference of this magnitude with a power of 80 % and a two-sided alpha of 0.05. After allowing for a conservative loss to follow-up of 15 % [31], we calculated that we will need to recruit 210 participants (105 per group). A defined secondary outcome for this trial is cognitive performance 1 week and 3 months after surgery. A study with 100 participants per group at the 3-month follow-up will have 81 % power to declare as significant between group difference of 2 points in the change from baseline score of the TICS-m (1 versus 3 points, SD 5). A change of less than 2 points would be of uncertain clinical significance.

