### Trial design

The Healthy Heart-Mind trial is a randomized, double-blind, placebo-controlled clinical trial of 3 mg melatonin or matching placebo administered on seven consecutive days for the prevention of delirium following cardiac surgery (two arms, 1:1 allocation, parallel design). This study follows SPIRIT guidelines, and the relevant checklist is available as an additional electronic file (Additional file 1). 

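### Recruiting 210 and losing the stated 15% leaves about 178 participants, short of the 182 the plan requires; the target matches 182 × 1.15, not 182 / 0.85

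*Protocol article*

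**What the plan says.** The Sample size section of the protocol article builds the recruitment target in two steps.

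- **Evaluable number.** It assumes a "conservative 25 % incidence of delirium in the control group" and "an incidence of 9.4 % in the intervention group". The calculation is made "with a power of 80 % and a two-sided alpha of 0.05", and the result is that "we will require 91 participants per group (182 participants in total").
- **Allowance for loss.** "After allowing for a conservative loss to follow-up of 15" per cent, the section gives the target: "we calculated that we will need to recruit 210 participants (105 per group").

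The inflation formula is not printed. Participants and setting repeats the figure ("We will recruit 210 participants undergoing elective or semi-elective cardiac surgery in Perth, Western Australia"), and so does the abstract. Trial design fixes equal arms ("two arms, 1:1 allocation, parallel design").

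**The concern.** An allowance for loss has one purpose: to leave the required number once the expected losses have occurred. If a fraction *d* is lost, the target must therefore be the required number divided by (1 − *d*). Multiplying by (1 + *d*) takes the percentage of the wrong base and always falls short. The stated 105 and 210 look like the product of that multiplication.

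The calculation concerns the primary outcome. If the target is too low, the trial does not reach the evaluable number, or the 80% power, that the section claims under its own assumptions. The section's 91 per group is the smallest whole number that satisfies the formula behind it, so it holds no hidden margin to cover the gap.

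**Working it through.** **Inputs**, all from the protocol article: control incidence p₁ = 0.25; intervention incidence p₂ = 0.094; two-sided alpha 0.05; power 80%; 91 per group (182 in total) required; loss 15%; target 210 (105 per group), all from Sample size; 1:1 allocation from Trial design.

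**Step 1: reproduce the 91 per group.** The two-proportion formula with pooled variance under the null and no continuity correction is

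n = [z₀.₉₇₅ √(2p̄(1−p̄)) + z₀.₈₀ √(p₁(1−p₁) + p₂(1−p₂))]² / (p₁ − p₂)²

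- p̄ = (0.25 + 0.094)/2 = 0.172, so √(2 × 0.172 × 0.828) = 0.5337
- √(0.25 × 0.75 + 0.094 × 0.906) = 0.5222
- n = (1.960 × 0.5337 + 0.8416 × 0.5222)² / 0.156² = 90.7, rounded up to 91 per group

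This matches the plan.

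**Step 2: reproduce the 210.**

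| Method | Per group | Total |
|---|---|---|
| Multiply by 1.15 | 91 × 1.15 = 104.65, up to 105 | 182 × 1.15 = 209.3, up to 210 |
| Divide by 0.85 | 91 / 0.85 = 107.06, up to 108 | 182 / 0.85 = 214.1, up to 215 (216 with equal arms) |

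The first row gives both stated figures exactly. The second row gives neither.

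**Step 3: what 210 delivers.**

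- 210 × 0.85 = 178.5, or 105 × 0.85 = 89.25 per group. In whole participants that is 178, or 89 per group.
- Shortfall against 182: 182 − 178.5 = 3.5 participants, about 2 per group.
- Largest loss at which 210 still leaves 182: 1 − 182/210 = 13.3%.

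**Step 4: effect on power.** With the same formula solved for power,

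power = Φ{[(p₁ − p₂)√n − z₀.₉₇₅ √(2p̄(1−p̄))] / √(p₁(1−p₁) + p₂(1−p₂))}

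| Evaluable per group | Power |
|---|---|
| 91 | 80.1% |
| 90 | 79.7% |
| 89 | 79.3% |

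One participant fewer per group than 91 already takes power below 80%.

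**The case against.** Four points can be made for the plan.

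1. **The effect is tiny.** Power falls by 0.8 of a percentage point, and 215 to 216 is within 3% of 210. This is right, and it limits the weight of the finding. It does not make the three printed figures consistent.
2. **Other standard formulas need fewer participants.** With the same inputs the unpooled and arcsine formulas each need 88 per group, which 89 would meet. But the continuity-corrected formula needs 104, so the choice of formula cuts both ways. The plan's 91 is what the pooled, uncorrected formula gives, and the comparison has to be with the plan's own requirement.
3. **Loss for the primary outcome may be well under 15%.** Delirium is assessed daily in hospital up to day 7 or discharge, and the Statistical methods section plans a panel model that uses all available assessments. Loss is more likely at the 3-month contact. This is plausible, and the real effect on primary-outcome power may be smaller than calculated here. However, the Sample size section applies 15% to this very calculation and gives no separate in-hospital rate.
4. **The multiplier is inferred.** The article does not print the inflation formula. The match to both 105 and 210 makes the inference strong, but the finding does not need it: by whatever route 210 was reached, 210 less 15% is not 182.

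**Conclusion.** The concern holds. The requirement (182), the loss rate (15%) and the target (210) in the Sample size section are mutually inconsistent, and nothing elsewhere in the article reconciles them. Under the plan's assumptions the trial ends with about 178 evaluable participants (89 per group) and 79.3% power, against the 182 and 80% it states.

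The power figure rests on incidences of 25% and 9.4%, the full 15% being lost to the primary outcome, and the pooled uncorrected formula. The shortfall in numbers rests on the printed figures alone. The trial is not materially underpowered for this reason, but the stated numbers are wrong as written and should be corrected.

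**What to change.** Replace the last step of the primary-outcome calculation with figures that agree. Either of these does so without changing recruitment:

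- State what 210 delivers: 210 recruited, about 178 evaluable after 15% loss (89 per group), 79% power.
- State the loss that 210 can absorb: up to about 13% (1 − 182/210) while keeping 182 evaluable. This replaces the 15% assumption, so it should come with a reason, such as the short in-hospital assessment period.

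The cost is one sentence and a slightly less favourable stated power or loss allowance. If the sponsor prefers to keep both 15% loss and 80% power, the consistent target is 216 (108 per group), six more than planned. The Trial status section says recruitment had not begun, so that option was open when the article was written. The 210 in the abstract and in Participants and setting would then change too.

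While editing the paragraph, also check the statement on the cognitive outcome. It assumes 100 per group at 3 months, whereas 105 per group less 15% leaves about 89.

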### Statistical methods

We will analyze and store the data using reliable statistical software (Stata, StataCorp, College Station, TX, USA). Baseline data will be compared using descriptive statistics, Student *t* tests for normally distributed continuous variables, the Mann-Whitney test for ordinal variables and Pearson’s chi-square statistic for categorical variables. The primary outcome analysis will be intention-to-treat and will use multilevel logistic regression of panel data (xtlogit). This approach to the analysis of the data allows for the inclusion of all available information and for the investigation of interactions between terms (such as intervention and time). A similar approach will be used to analyze other binary outcomes (e.g., use of psychotropic medication). We will use multilevel mixed models to investigate changes in scores of the MDAS and TICS-m (continuous variables). All probability tests will be two-tailed and will be declared as significant when *p* < 0.05.

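### The 81% power quoted for the 3-month TICS-m outcome assumes 100 per group, but the plan's own 105 recruited per group and 15% loss leave about 89 and about 76% power

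*Protocol article*

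**What the plan says.** All the figures stand in one paragraph, the Sample size section of the protocol article.

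- **Recruitment and loss.** The primary outcome needs 91 per group. "After allowing for a conservative loss to follow-up of 15" per cent, the authors write, "we calculated that we will need to recruit 210 participants (105 per group").
- **Cognitive outcome.** Cognitive performance is then named as a defined secondary outcome. The power sentence opens with the number it assumes, "A study with 100 participants per group at the 3-month follow-up will have", and the result it reports for that number is "81 % power to declare as significant between group difference of 2 points in the change from baseline score of the TICS-m". The assumed changes and their spread are given in brackets: "1 versus 3 points, SD 5". The paragraph adds that a change below 2 points would be of uncertain clinical importance, so 2 points is the chosen threshold.
- **Test level.** The primary calculation uses "a two-sided alpha of 0.05". Statistical methods extends this to the rest: "All probability tests will be two-tailed and will be declared as significant when" p is below 0.05.
- **Analysis.** Statistical methods says: "We will use multilevel mixed models to investigate changes in scores of the MDAS and TICS-m (continuous variables"). TICS-m is measured at baseline, discharge and 3 months.

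**The concern.** The number analysed at 3 months does not follow from the number recruited and the loss allowed for. If 105 per group are randomized and 15% are lost, 100 per group cannot remain. The figure of 100 also differs from the 91 evaluable per group that the primary calculation aims for. No section gives a separate, lower loss rate for 3 months.

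A reader will take 81% as the power of this trial, because the sentence sits in the sample size justification and the Discussion later calls the trial adequately powered. If the plan's own loss rate applies, the chance of missing a true 2-point difference is about 24%, where the paragraph implies 19%.

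**Working it through.** **Inputs, all from the protocol article.** Difference 2 points, SD of change 5, two-sided alpha 0.05, 1:1 allocation, 105 recruited per group, 15% loss, 100 per group stated at 3 months.

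**Step 1: reproduce the stated power.** For two equal groups of size n, the standard error of the difference is 5 × √(2/n). Power by the normal approximation is Φ(2/SE − 1.96).

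- n = 100: SE = 5 × √(2/100) = 0.707; 2/0.707 = 2.828; Φ(2.828 − 1.960) = Φ(0.868) = 80.7%.
- The noncentral t distribution gives 80.4%.
- A one-sided test would give 88.2%, so the stated figure is two-sided.

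The 81% is therefore reproduced. The formula is sound, and what needs checking is the n.

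**Step 2: the n that the plan's own figures give.**

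- Remaining at 3 months: 105 × (1 − 0.15) = 89.25, about 89 per group.
- Loss at which 100 remain: 1 − 100/105 = 4.8%.
- Recruitment that would leave 100 after 15% loss: 100/0.85 = 117.6, so 118 per group (236 in total).

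**Step 3: power at that n.**

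- n = 89: SE = 5 × √(2/89) = 0.750; 2/0.750 = 2.668 (unrounded SE); Φ(2.668 − 1.960) = Φ(0.708) = 76.1%. Noncentral t: 75.6%.
- Difference detectable with 80% power, (1.960 + 0.842) × SE: 2.802 × 0.707 = 1.98 points at n = 100, and 2.802 × 0.750 = 2.10 points at n = 89.

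**Step 4: sensitivity to the loss at 3 months.**

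| Per group at 3 months | Loss from 105 | Power (t) | Power (normal) |
|---|---|---|---|
| 100 | 4.8% | 80.4% | 80.7% |
| 97 | 7.6% | 79.2% | 79.6% |
| 94 | 10.5% | 77.9% | 78.3% |
| 91 | 13.3% | 76.5% | 77.0% |
| 89 | 15.2% | 75.6% | 76.1% |

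**Step 5: does the way the 15% was applied matter?** The 210 equals 182 × 1.15 = 209.3, rounded up to an even number. Dividing instead, 182/0.85 = 214.1, gives 215 in total, or 108 per group. Even then 108 × 0.85 = 91.8, about 92 per group. Neither way of applying the 15% gives 100.

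**Step 6: what a baseline covariate could add.** This concerns the optional improvement only. If TICS-m has the same variance at baseline and follow-up, with correlation ρ between them, the SD of change is σ√(2(1 − ρ)) and the residual SD after adjustment is σ√(1 − ρ²). The ratio is √((1 + ρ)/2), so the residual SD is 5 × √((1 + ρ)/2). The document gives no ρ, so a range is assumed. Power at 89 per group is by noncentral t:

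| Assumed ρ | Residual SD | Power |
|---|---|---|
| 0.5 | 4.33 | 86.5% |
| 0.6 | 4.47 | 84.3% |
| 0.7 | 4.61 | 82.1% |
| 0.8 | 4.74 | 79.9% |
| 0.9 | 4.87 | 77.7% |

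**The case against.** **The sentence is conditional and true.** It says what a study with 100 per group would have, and that is correct. It never says that 105 less 15% is 100. This stands: a reader might infer that the power was miscalculated, and it was not. But the sentence specifies the number at the 3-month follow-up and serves as justification for this trial's size, so the 100 has to be attainable under the assumptions around it.

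**The 15% was set for the primary outcome.** It is called conservative, is cited to a trial in acutely ill medical in-patients, and enters the calculation for the 7-day outcome. Carrying it to 3 months is an inference. The section on measuring morbidity and lifestyle says that TICS-m, which can be given by telephone, was chosen partly to help retention. If loss at 3 months were about 5% or less, the 81% would stand. However, 15% is the only rate given, and no figure supports a lower one at the later visit. A reader might go further and assert that losses and deaths at 3 months will exceed those at 7 days. That is plausible, but the document gives no 3-month loss or mortality figure, and the point does not need it.

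**The analysis may be more efficient than the power calculation.** A reader might infer that the trial commits to raw change scores and so discards precision. The text does not support that. It plans multilevel mixed models, and how baseline enters them may properly be left to the statistical analysis plan, which is not at hand. Using the SD of change to size a study is conventional.

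**The consequence is small.** This also stands. The outcome is secondary, it does not set the sample size, and a null result would be judged mainly from its confidence interval.

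**Conclusion.** The point holds as an inconsistency between stated numbers. On the plan's own recruitment and loss, about 89 per group remain at 3 months. Power for a 2-point difference is then about 76%, some 5 percentage points below the stated 81%, and the difference detectable with 80% power moves from 1.98 to about 2.1 points.

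The conclusion rests on two assumptions: that the 15% loss applies at 3 months, and that the comparison is the simple two-group one which reproduces the stated figure. It does not show any fault in the power formula, and it does not bear on the size of the trial for delirium.

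A reader might also conclude that a baseline covariate would restore the stated power. That cannot be promised: over assumed correlations of 0.5 to 0.9, power at 89 per group runs from about 87% down to about 78%, under an equal-variance assumption that the document does not address.

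**What to change.** Make one of two changes to the sentence in Sample size:

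1. Restate it, for example: *with 15% loss, about 89 per group at 3 months give about 76% power for a 2-point difference, SD of change 5*; or
2. Keep 100 per group and 81%, and state and justify a 3-month loss of 5% or less.

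Either costs one sentence, with no extra participants or data.

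Optionally, add one line to Statistical methods or the statistical analysis plan that names baseline TICS-m as a covariate in the planned mixed model, or constrains the baseline means to be equal. Any power claimed from this should state the assumed correlation and show the range.
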